**A5 Proposed start date and duration in months.**

Sensitisation and preparation in August, recruitment September to December 2004, follow-up to January 2005, lab work and data processing to August 2005.

**A6 Summary of project, long term objectives and specific aims (not more than 200 words)**

This section is very helpful to the Committees in determining quickly the main features of the study, and should be as clear and concise as possible. It should cover the key objectives and endpoints and, if the project is hypothesis driven, then the hypothesis should be stated here.

Despite worsening drug resistance, treatment policy for malaria still relies on chloroquine in most West African countries. Lapdap is an affordable and effective drug, but patients with glucose-6-phosphate dehydrogenase (G6PD) A- deficiency are more susceptible to the haemolytic effects of the dapsone component of Lapdap, therefore there is a need to evaluate the extent to which the risk associated with the use of the drug in settings without G6PD screening might outweigh the benefits to malaria treatment. Lapdap acts in a similar way to sulfadoxine-pyrimethamine (S-P) but appears effective against certain S-P-resistant parasites, it is therefore of interest to investigate possible association of Lapdap treatment failure with carriage of S-P-resistant genotypes, and the transmissibility of these genotypes after treatment with Lapdap. Artemisinin combinations are recommended by WHO but the alternatives need to be evaluated in operational settings, because compliance, which affects efficacy and the selection of resistant parasites, may be an important factor in discriminating between alternative treatments. Co-artemether is effective in a supervised 6-dose regimen but its effectiveness when doses are unsupervised has not been evaluated. We will evaluate, in operational settings, the safety and effectiveness of Lapdap and co-artemether for treatment of uncomplicated malaria in patients 6months to 10years.

**A8 Checklist/Signatures**

**Please complete the following checklist and comment as appropriate.** This section is designed to ensure that all the planning steps have been taken that are needed for a successful project and that the resource requirements are appropriately laid out in Section D. For projects at the MRC Laboratories, Programme Heads will help visiting workers, and others preparing proposals at a distance, to ensure liaison with key individuals who need to be consulted locally.

1. **Has the project been discussed and cleared with the institutions in which research will be carried out including health services to which the study will need access?**

Initial discussions have been held with National Malaria Control Programme, AFPRC Hospital Farafenni and the North Bank East DHT. Discussions have been planned with Njaba Kunda and Brikama health centres.

1. **Have all investigators and collaborators given their agreement to take part in the study as described?**

Yes

1. **Have ethical issues been addressed?** Give details in section C**.**

Yes

1. **Does the project require laboratory work, new laboratory procedures, or the riding of motorcycles? Have the safety issues been addressed?** (The Health and Safety Manager will advise on risk assessment)

Yes

1. **Will the project require data and/or materials to be taken out of The Gambia? If so please give details and sign the following statements:**

Plasma samples will be sent to the London School of Hygiene and Tropical Medicine for the testing of drug levels seven days after treatment. If the molecular techniques required for some of the analysis are not established in The Gambia before the study gets underway then filter papers will be analysed in the London School of Hygiene and Tropical Medicine.

The principal investigator undertakes to leave with the Computer Centre data archivist in The Gambia, a complete copy of the data set at the following two time points:

1. After data entry and verification (“raw data sets”)
2. At the point of submission for publication of final report (“analysis data sets”)

**B1 Background**

The background should show the relationship between the proposed study and the present state of knowledge and should reference previous work by the investigators and others. The results of any pilot experiments should be stated.

Malaria remains one of the most common causes of morbidity and mortality in Gambian children. In rural areas of The Gambia, about 1 in 25 children die from malaria before reaching the age of 5 years. Malaria management has relied upon prompt treatment of clinical attacks with chloroquine (CQ), the most affordable antimalarial drug, delivered through the primary health care system. Treatment at Government health centres is free for children under 5 years. Older children and adults pay a token fee of 1 and 5 Dalasis, respectively. Resistance of *Plasmodium falciparum* to chloroquine has become increasingly common since first reported in the Gambia in 1986 (Menon, 1987). In a study in 2002 in Brikama health centre, (unpublished data), 28% of children treated with CQ failed to show an adequate response by day 14. In The Gambia some clinics give CQ combined with sulfadoxine-pyrimethamine, but there has been no change in the Government’s antimalarial treatment policy due to concern about the impact on availability of increased costs. Since CQ resistance is already common, widespread use of SP in combination with CQ is likely to lead to rapid spread of SP resistance; both drugs when used alone lead to a high prevalence of gametocyte carriage among treated patients, so CQ+SP will not prevent transmission of CQ- and SP-resistant parasites from treated cases. CQ is also not useful as a partner drug in combination with other antimalarials (Sutherland et al. 2003). There is therefore an urgent need to evaluate alternative combination treatments. The rational choice of combination treatment depends on safety, tolerability and efficacy, on the characteristics of the treatment for limiting the spread of resistance, and on cost effectiveness. Effectivenss trials in operational settings are important because adherence may vary and this may be important in discriminating between alternative combinations. Combination treatment with artemisinin and a longer-acting partner drug is the strategy recommended by WHO but these combinations are costly. The combination of chlorproguanil (=lapudrine) and dapsone (Lapdap) has been developed as a fixed-dose tablet primarily for the treatment of semi-immune patients in tropical Africa. It is safe and efficacious in controlled trials with supervised doses (Winstanley, 2001; Lang and Greenwood 2003). It has been registered by the UK Medicines and Healthcare Products Regulatory Agency (MHRA) and also by a number of African countries. At a cost (at the factory) of 9 US cents per course, Lapdap is an affordable alternative to CQ. However, since patients with glucose-6-phopsphate dehydrogenase (G6PD) A- deficiency are more susceptible to the haemolytic effects of the dapsone component of Lapdap, it is important to evaluate the extent to which the risk associated with the use of the drug in settings without G6PD screening might outweigh the benefits to malaria treatment.

Lapdap acts in a similar way to SP, by inhibition of the enzyme dihydrofolate reductase (DHFR). Resistance to pyrimethamine is conferred by simple point mutation of the gene for DHFR (Plowe et al, 1996). It is likely that there is a small but constant rate of mutation of this gene during the parasite’s sexual cycle. Only those mutations conferring benefit surviving to predominate. In the presence of selection pressure of antifolate drug, mutations of DHFR which reduce sensitivity to the drugs tend to be selected during the asexual cycle in the human host, and then pass on to the next host via the mosquito vector. Four point mutations are particularly important, at codons 108, 51, 59 and 164. In Africa the DHFR drug resistant phenotype is initiated by mutation at 108, followed by mutations at 51 and 59; the triple mutant 108+51+59 is associated with poor clinical response. All three mutations occur in The Gambia but their prevalence is not known. Lapdap appears effective against some SP-resistant parasites and is likely to exert less selection pressure than SP because of its shorter half-life. It is therefore of interest to examine possible association of these mutations with Lapdap treatment failure and also to measure the frequency and transmissibility of these genotypes after Lapdap treatment.

Co-artemether is a fixed-dose combination that has been shown to be safe and efficacious in supervised trial conditions. Following findings that the 4-dose regimen produced only 76% cure rates by day 28 in Thailand, compared to 97% for the 6-dose regimen, WHO are recommending the 6-dose regimen. Since compliance to this complex regimen may be poor in operational settings it is important to evaluate coartemether when doses are unsupervised. We therefore propose to compare the effectiveness of Lapdap and Co-artemether for treatment of uncomplicated malaria in an operational setting. We will also investigate acceptability of the treatments and compliance, the safety of treatment in G6PD-deficient and normal malaria patients, the effects of treatment on transmissibility of P.falciparum, the cost effectiveness of the two treatments.

### B3 Project description

This should cover project plan, time-scales, descriptions of methods, justification, analyses to be carried out, expected outcomes (see also B4 and B5 where particular details need to be set out and cross refer as necessary).

**Study design and methods**

*Study area and study population*

Patients will be recruited from three health centres, Farafenni Maternal and Child Health (MCH) Clinic, which serves the rural town of Farafenni; Njaba Kunda, a mission clinic in a rural village; and Brikama Health Centre, a Government health centre serving a large urban community. Children aged 6 months to 10 years presenting at health centres with a history of illness, who have a fever or recent history of fever, will be screened and those with uncomplicated malaria, a positive blood smear with a parasite density 2000 to 200,000 parasites/μl, monoinfection with *P. falciparum*, and a packed cell volume of >=20%, will be invited to enrol into the study after written informed consent is given

*Treatment and follow-up*

The study patients will be randomised to receive three daily doses of Lapdap, or a six-dose course of co-artemether. Dosages will be determined according to manufacturers’ instructions. The first dose will be given by the mother under direct observation of the dispensing nurse, and subsequent doses will be given at home unsupervised. The parent/carer will be encouraged to bring the child back to clinic if the child’s condition does not improve

The parent/carer will be visited at home a day after the last dose should have been taken (Day 3) in order to check any left over medication, to ask about compliance and adverse reactions and to collect finger prick blood samples for haemoglobin check using Hemocue (portable haemoglobin analyser machine. Haemoglobin results will be entered in lab forms pre-printed with Day 0 haemoglobin results. Patients with severe anaemia (Hb 5 g/dl) or Hb that has fallen by 2g/dl or more from the Day 0 measurement will be promptly referred to the clinic for treatment. Nurses and drivers will be placed on 24-hour emergency duty at the health centres/hospital where the study is sited to handle emergencies. Recruitment will be limited to 5-8 kilometre radius of the study site for quick access to a clinician in the case of an emergency.

The parent/carer will be requested to return the patient to the clinic on day 14 and day 28 after treatment for clinical evaluation and blood sampling for PCV, microscopy and molecular analysis. In one centre, Farafenni, post-treatment transmission of resistant genotypes of *P.falciparum* will be evaluated in transmission experiments, by membrane feeding of post-treatment samples to mosquitoes. In addition to randomization for treatment, subjects in Farafenni will be randomized to be checked for gametocytaemia on either day 7 or day 14 after treatment. Subjects who are gametocyte positive will be asked to give a venous blood sample for mosquito feeds. Samples will be used for feeding to 5-day-old *Anopheles gambiae s.s.* via an artificial membrane, and mosquito midguts dissected 7-8 days later to determine the number of malaria oocysts. The protocol allows assessment of the possible effects of drug or antibodies in the blood meal on transmission. DNA will be extracted from oocysts to determine the presence of genotypes associated with resistance to sulfadoxine and pyrimethamine.

From the finger-prick blood samples collected on filter paper at screening and from samples taken from parasitological treatment failures, 10-20μl aliquots will be tested using nested PCR on extracted DNA to detect point mutations in genes associated with resistance to sulfadoxine-pyrimethamine DHFR (codons 51, 59, 108) and DHPS (codons 437, 540), in order to examine their possible association with Lapdap treatment failure. In addition, if a child has a second episode of parasitaemia, samples from the first and second episode will be assayed for the three sequence families of MSP1 block 2 repeat region and the two sequence families of the MSP2 repeat region, to distinguish recrudescence from reinfection. Since patients with glucose-6-phosphate dehydrogenase (G6PD) A- deficiency are more susceptible to the haemolytic effects of the dapsone component of Lapdap, in this trial we will determine the G6PD genotype using an ARMS PCR technique. Retrospectively, we will screen for the two A- associated mutations, an A to G transition at position 376, encoding the B (normal) to A change (Asn126Asp), and a G to A transition at position 202, encoding the specific A- change (Val68Met), and we will also measure enzymatic activity, in order to evaluate the extent to which the risk associated with the use of the drug in settings without G6PD screening might outweigh the benefits to malaria treatment.

In addition we will measure concentrations of drug components in a sample of day 0 samples and in day 7 samples, using the HPLC method at LSHTM, as a verification of compliance with treatment. An economic component to the studies will be incorporated to assess provider costs as well as social costs associated with treatment and with treatment failure. Qualitative research techniques will be used to investigate mothers’ perceptions of antimalarial treatment and operational issues.

*Endpoints, sample size, randomization, and data management*

The primary endpoint will be clinical and parasitological cure by day 28. Secondary endpoints include the incidence of clinical anaemia at any time during the 28 day follow up, defined as clinical signs of anaemia and Hb that has fallen by 2g/dl or more from the day0 measurement; and change in Hb from day0 to day 28; and percentage transmission on day 7 and day 14 after treatment.

The trial will not be blinded, but the randomization procedure will ensure concealment of the allocation sequence. Databases will be designed in Access.

A Data Safety Monitoring Board will being convened for the trial. The local safety monitor is [name].

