**(b) Summarise the potential risks and benefits to individuals, communities or country**

Although dapsone (one of Lapdap’s constituents) remains widely used in Africa against leprosy, it produces dose-related haemolysis that can be severe in patients with glucose-6-phosphate dehydrogenase (G6PD A-) deficiency. Anaemia is consequently the most common adverse event associated with Lapdap (Pincock 2003). It is therefore important to evaluate the extent to which the risk associated with the use of the drug in settings without G6PD screening might outweigh the benefits to malaria treatment. In the normal pattern of G6PD deficiency no evidence of haemolysis is apparent until 48-96 hours after substance ingestion. Therefore, the child will be visited at home on day 3 (the day after the last dose of medication should have been taken) by a fieldworker who will ask parent/care giver about the child’s condition, will check for signs of anaemia and haemolysis (pallor and jaundice) and collect finger prick blood sample for haemoglobin analysis. If the child is anaemic or not well he/she will be referred to the clinic for further evaluation and prompt treatment. All participants will have ready access to emergency treatment when adverse events develop. Both Lapdap and the 6-dose regimen of Co-artemether have been shown to be safe and effective under strictly controlled trial conditions but it is not known to what extent poor adherence to the recommended regimens will affect efficacy. Trials in operational settings may help discriminate between the choice of treatment. There are no risks to participating communities or country

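### The only anaemia incidence endpoint needs clinical signs as well as a 2 g/dl haemoglobin fall, so in an open-label trial measured falls without recorded signs go uncounted

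*Protocol*

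**What the plan says.** The endpoints paragraph of Protocol B3 states: "Secondary endpoints include the incidence of clinical anaemia at any time during the 28 day follow up", and the event is "defined as clinical signs of anaemia and Hb that has fallen by 2g/dl or more from the day0 measurement". The other haemoglobin endpoint listed is "change in Hb from day0 to day 28". The same part of B3 says: "The trial will not be blinded, but the randomization procedure will ensure concealment of the allocation sequence".

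The treatment and follow-up paragraph of B3 plans a home visit on day 3 with a Hemocue reading, entered on a form that already carries the day 0 value. A child is acted on for severe anaemia (given at 5 g/dl; the comparison sign is not legible in the text available) "or Hb that has fallen by 2g/dl or more from the Day 0 measurement will be promptly referred to the clinic for treatment". No clinical signs are needed for that referral.

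Entry is allowed at "a packed cell volume of >=20" per cent. Section C(b) says that on day 3 a fieldworker "will check for signs of anaemia and haemolysis (pallor and jaundice) and collect finger prick blood sample for haemoglobin analysis". It also says that haemolysis is not apparent until 48-96 hours after ingestion.

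**The concern.** Whether haemolysis on Lapdap, used without G6PD screening, outweighs its benefit is a stated purpose of the trial (A6, B1, B3, C(b)). C(b) calls anaemia the most common adverse event linked to the drug. The only incidence endpoint for that question joins an objective measurement to a judgement by AND.

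This has two consequences. Falls that were measured but not accompanied by recorded signs drop out of the count. And the judgement is made by people who know the treatment: the day 3 visitor also checks the left-over medication, no blinded assessor is described, and no criteria for grading signs are given. If signs are looked for or noted more readily in one arm, the between-arm comparison is distorted although the haemoglobin values are sound.

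**Working it through.** The protocol gives no event rate, power or sample size for anaemia, so there is no figure of its own to reproduce. The check is mainly one of logic.

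**1. The definition against the day 3 rule.**

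| Finding on day 3 | Referred (B3, follow-up) | Counted as an event (B3, endpoints) |
|---|---|---|
| Fall of 2 g/dl or more, signs recorded | yes | yes |
| Fall of 2 g/dl or more, no signs recorded | yes | no |
| Severe level reached by a fall under 2 g/dl, with or without signs | yes | no |

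The second row applies at any baseline and to a fall of any size. The third row is limited by the entry floor, as follows.

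**2. Width of the severe-anaemia gap.** Inputs are the PCV floor of 20% (B3, B4) and the severe level of 5 g/dl (B3). The conversion Hb = k × PCV is my assumption, with k = 1/3 and a range of 0.30 to 0.34.

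- Hb at the floor: 20 × 1/3 = 6.67 g/dl (range 6.0 to 6.8).
- Fall needed to reach 5 g/dl: 6.67 − 5 = 1.67 g/dl (range 1.0 to 1.8), always under 2.
- Upper edge of the band: 5 + 2 = 7.0 g/dl, or PCV 7.0 ÷ (1/3) = 21.0% (range 20.6% to 23.3%).

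The gap therefore concerns children entering at about PCV 20-21%, and at most up to about 23%.

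**3. Whether the day 28 endpoint fills the gap.** Doses fall on days 0 to 2. A window of 48-96 hours ends on day 4 counted from the first dose, and on day 6 counted from the last. Day 28 is 28 − 4 = 24 or 28 − 6 = 22 days later. By then a child may have recovered or been treated, and a mean change is not an incidence. The day 3 reading, about 72 hours after the first dose, lies inside the window counted from that dose.

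**4. Illustration of events lost (assumed rates).** With equal allocation (assumed) and the planned 10% loss, 1180 × 0.9 ÷ 2 = 531 children per arm are evaluable. Suppose true falls of 2 g/dl or more occur in 10% and 5%, and a share s of them also has recorded signs. The counted risks are then 0.10s and 0.05s. Power at two-sided 0.05 is Φ[(difference − 1.96 × SE₀) ÷ SE₁], where SE₀ uses the pooled and SE₁ the separate proportions.

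| s | Counted risks | Power |
|---|---|---|
| 1 (all measured falls) | 10% v 5% | 87% |
| 0.7 | 7% v 3.5% | 73% |
| 0.5 | 5% v 2.5% | 57% |
| 0.3 | 3% v 1.5% | 38% |

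**5. Illustration of bias (assumed recording rates).** The apparent risk ratio equals the true ratio multiplied by s(Lapdap) ÷ s(co-artemether). With equal true risk:

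- 60% v 50% gives 0.60 ÷ 0.50 = 1.2.
- 70% v 50% gives 1.4.
- 60% v 40% gives 1.5.
- 50% v 60% gives 0.83.

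The direction is not known in advance.

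**The case against.** The endpoint is secondary and is labelled clinical anaemia, so requiring signs is part of the idea. The list is introduced by a word that leaves room for other summaries, and it includes an objective haemoglobin change. All of this stands. It argues for keeping the clinical endpoint, but not for having it as the only incidence measure.

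A reader might infer that the referral rule and the endpoint contradict each other. They do not. One is a sensitive safety trigger and the other is an outcome, and they may differ. Uncounted cases are still measured, recorded and referred, and a data safety monitoring board is planned. They are missing from one incidence count, not from the safety data.

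A reader might also infer that unblinded staff could create events. They cannot, because an objective fall of 2 g/dl or more is always required. Their judgement decides only whether a measured fall counts. On day 3 every such fall leads to a clinic visit in both arms, which gives a second chance to record signs, and C(b) names the signs as pallor and jaundice. This limits the bias but does not remove it, because the clinic is not blinded either.

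**Conclusion.** The point holds as a should-fix improvement. As written, the only anaemia incidence endpoint leaves out measured early falls without recorded signs and lets unblinded judgement select among measured falls. The day 28 change comes too late to make up for this.

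It would be tempting to say that the definition drops the most severe cases among the most anaemic children. The documents do not support that. The severe-anaemia gap needs an entry PCV of about 20-21% (assuming Hb = PCV/3) and a fall under 2 g/dl. A larger fall in the same child meets the haemoglobin condition. The protocol does not say how many children enter in that band.

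The power and risk-ratio figures are illustrations only. They depend on how often signs are recorded and on true fall rates, and the documents give neither. The primary endpoint is not affected.

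**What to change.** Add a secondary endpoint: incidence, at any time during the 28 days, of haemoglobin at the protocol's own severe-anaemia level OR a measured fall of 2 g/dl or more from day 0, regardless of signs. Take the day 3 Hemocue value as the key reading, and make this the main between-arm comparison of anaemia incidence. Keep the signs-plus-fall endpoint and report it alongside.

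State how haemoglobin is obtained on days 14 and 28. B3 names PCV at those visits, B4 says PCV or haemoglobin, and Hemocue is specified only for day 3. If a conversion from PCV is to be used, write it down, and confirm that the day 0 value is comparable with the day 3 reading. The B4 list of finger-prick days should also show day 3, which B3 and C(b) already plan.

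The cost is a short edit to the endpoint text and, for day 3, no data beyond those already planned. The event count will be higher and will include mild falls without symptoms. Because B4 plans to pool countries for the G6PD and anaemia analysis, the added definition should be agreed with the other participating countries. No referral or treatment rule changes.
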